#### 2.10.3. Statistical analyzes

The data analysis followed the principle of intention-to-treat (ITT). The primary outcome will be compared between the two arms using the analysis of covariance for adjusted analysis, with ALSFRS-R at baseline as the covariate in the model and HLSJ group as the fixed effect. The least squares mean (LSMEAN) and its 95% confidence interval (CI) will be measured. If the lower limit of the 95% CI of the LSMEAN difference between the HLSJ and riluzole group is greater than zero, the HLSJ group will be considered superior to the riluzole group. Intra-group changes from baseline will be tested using the Wilcoxon signed-rank test. Wilcoxon rank-sum test will be used in the test of between-group differences in changes.

A similar approach will be used to analyze the secondary outcomes. Wilcoxon rank sum test (ordered categorical data) or the Cochran–Mantel–Haenszel statistics with controlled central effects will be conducted between the two groups for categorical data. We also computed the risk difference (RD) and its 95% CI. For time-to-event data, the product-limit method will be used to calculate the quartiles and two-sided 95% CI of time to each endpoint event. The Kaplan–Meier curve will be constructed and analyzed using log-rank tests.

All safety data will be documented according to the System Organ Class and Preferred Term. Subgroup analyzes will be conducted according to clinical stratification (e.g., bulbar or limb onset). The last observation carried forward (LOCF) method will be performed to impute missing values of the primary outcome measure. Missing values for secondary outcomes and safety will not be processed with a similar approach. Once the database is locked, the statistical analysis plan will not be revised. Then, the statistical analysis will be performed using SAS V9.4. In all statistical analyzes, *p*-values <0.05 are considered statistically significant with two-sided test.

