### 2.9. Outcomes

#### 2.9.1. Primary outcome

The primary outcome was the change in ALSFRS-R scores from baseline to Week 48.

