#### 2.9.2. Secondary outcomes

The secondary outcomes of the study include the following:Changes in ALSFRS-R from baseline to Week 12, 24, and 36.Changes in Rasch-Built Overall Amyotrophic Lateral Sclerosis Disability Scale (ROADS) scores from baseline to Week 12, 24, 36, and 48.Changes in the percentages of measured to predicted values of FVC from baseline to Week 12, 24, 36, and 48.Changes in 40-item Amyotrophic Lateral Sclerosis Assessment Questionnaire (ALSAQ-40) scores from baseline to Week 12, 24, 36, and 48.Changes in the SSCMS from baseline to Week 12, 24, 36, and 48, and the efficacy of Chinese medicine syndrome.The rate of endpoint events and the time to endpoint events were defined as death, tracheostomy, or permanent-assisted ventilation (>22 h daily for >14 days).

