### 2.10. Statistical consideration

#### 2.10.1. Sample size calculation

The superiority test was performed for the comparison of the primary outcome in the two groups. Based on a previous real-world study of the long-term use of riluzole (Chen et al., 2016) and the consensus of the experts involved in the current study, we assumed that, for the changes of ALSFRS-R score, the adjusted mean superiority through 48 weeks between the HLSJ group and control group was 2.0 points, with a standard deviation of 4.0 points. Therefore, we needed to include 64 patients in each group (128 patients in total) to provide 80% statistical power with an alpha level of 0.05 in a two-sided test. Assuming an average dropout rate of 10%, recruitment of 144 patients will be necessary.

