### 2.11. Withdrawal criteria

Consent withdrawal or loss to follow-up means that the subjects withdrew from the trial.

For some reason, the subject is no longer suitable for the current trial. The investigators have the discretion to withdraw the subject from the trial if the following conditions occur:The health of the patient deteriorates or some serious complications occur.Abnormal liver function with one of the following conditions present: (1) ALT or AST >8 times the ULN; (2) ALT or AST >5 times the ULN for 2 weeks; (3) ALT or AST >3 times the ULN, with total bilirubin >2 times the ULN or INR >1.5; (4) ALT or AST >3 times the ULN, with the following conditions: fever, rash, nausea, vomiting, severe fatigue, right upper abdominal pain, and/or percentage of eosinophilic granulocyte increased (>5%).Neutrophile granulocyte in blood <2.0 × 10^9^/L.Some special physiological situation, such as a female who becomes pregnant.Allergy or serious adverse reaction.Subjects unblinded during the trial (except SUSAR).Other conditions, such as the subject refuses a necessary nasal feeding tube or gastrostomy.

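### LOCF for the Week 48 ALSFRS-R freezes dropouts and deaths at an earlier, usually better score, so the primary comparison favours the arm that loses more patients

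*Protocol article*

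**What the plan says.** Section 2.9.1 sets the endpoint: "The primary outcome was the change in ALSFRS-R scores from baseline to Week 48". In section 2.10.3 the primary comparison is made "using the analysis of covariance for adjusted analysis, with ALSFRS-R at baseline as the covariate in the model and HLSJ group as the fixed effect". Superiority is declared on this condition: "If the lower limit of the 95% CI of the LSMEAN difference between the HLSJ and riluzole group is greater than zero". The same section fixes the handling of missing data: "The last observation carried forward (LOCF) method will be performed to impute missing values of the primary outcome measure". It adds: "Missing values for secondary outcomes and safety will not be processed with a similar approach".

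Three other places bear on this.

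- Section 2.11 lets the investigator withdraw a patient on this ground, among others: "The health of the patient deteriorates or some serious complications occur".
- Section 2.9.2 brings death in only through the secondary endpoint events, "defined as death, tracheostomy, or permanent-assisted ventilation (>22 h daily for >14 days"). No separate rule for death is stated for the primary outcome.
- Table 2 schedules the ALSFRS-R at baseline and at Weeks 12, 24, 36 and 48. The full analysis set in section 2.10.2 requires at least one post-baseline efficacy evaluation.

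**The concern.** Carrying a Week 12, 24 or 36 score to Week 48 treats the patient as if progression had stopped. Take a patient who loses 3 points by the last visit and dies at Week 20. As the rule is written, that patient counts as a 3-point loss at Week 48, a better result than a survivor who lost 8.

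The missing values are not a random sample. Deterioration is a withdrawal ground, and the arms receive two different active drugs, with withdrawal grounds that include liver enzymes, neutrophils, allergy and serious adverse reactions. Dropout could therefore differ between arms.

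The rule feeds the trial's single superiority test. More or earlier loss on HLSJ would inflate its apparent benefit; more on riluzole would hide a real one. LOCF also treats imputed scores as observed, so the standard error does not reflect the missing information. The Week 12 to 36 scores of patients who complete are not used in the primary analysis at all.

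**Working it through.** **The plan's own figure.** Section 2.10.1 assumes that the difference "between the HLSJ group and control group was 2.0 points, with a standard deviation of 4.0 points", with 80% power and two-sided alpha of 0.05. A two-sample t-test needs 63.77, so 64 per arm (power 80.1%). 64 / 0.9 = 71.1, so 72 per arm and 144 in total. The sample size reproduces.

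**Critical difference.** With 72 per arm and SD 4.0, the observed difference needed for success is t(142) × 4 × √(2/72) = 1.977 × 0.667 = 1.32 points.

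**Assumptions not in the article.** Completers decline by D = 6, 9 or 12 points over 48 weeks. A dropout's last score is at Week 12, 24 or 36 with equal chance, so the mean fraction of follow-up missed is (0.75 + 0.50 + 0.25) / 3 = 0.5. Dropouts decline k times as fast as completers. Let Δ be dropout on HLSJ minus dropout on riluzole.

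**Closed form with no drug effect on the rate of decline.** In an arm with dropout d, the mean loss under LOCF is D[(1 − d) + dk/2]. Had dropouts been followed to Week 48, it would be D[(1 − d) + dk]. For HLSJ minus riluzole this gives:

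- LOCF estimate = Δ × D × (1 − k/2)
- true difference = −Δ × D × (k − 1)
- error = Δ × D × k/2

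**Dropouts decline at the same rate (k = 1), 15% vs 5%.** The bias is 0.10 × 6 × 0.5 = 0.30; 0.10 × 9 × 0.5 = 0.45; 0.10 × 12 × 0.5 = 0.60.

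**Simulation check.** ANCOVA on the LOCF change, 72 per arm, SD about 4, no true effect, 4,000 trials per cell. Each cell gives the mean estimate and the chance that the lower 95% limit exceeds zero.

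| Assumed decline | 10% vs 10% | HLSJ 15% vs 5% | HLSJ 20% vs 10% | HLSJ 30% vs 10% |
|---|---|---|---|---|
| 6 | −0.01; 2.8% | +0.30; 6.6% | +0.29; 5.6% | +0.60; 13.8% |
| 9 | −0.01; 2.5% | +0.45; 10.1% | +0.44; 9.3% | +0.88; 23.5% |
| 12 | +0.01; 2.8% | +0.59; 12.7% | +0.60; 12.3% | +1.20; 34.7% |

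**Reversed dropout (HLSJ 5%, riluzole 15%), true benefit 2.0 points.** For D = 6, HLSJ loses 4 × (1 − 0.025) = 3.90 and riluzole 6 × (1 − 0.075) = 5.55, a difference of 1.65. The simulated estimates for D = 6, 9 and 12 are 1.65, 1.50 and 1.36, with power of 69%, 58% and 46%.

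**Equal 10% dropout, true benefit 2.0 points.** 2.0 × (1 − 0.10 × 0.5) = 1.90, a mild attenuation.

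**Dropouts decline faster (20% vs 10%).**

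- k = 1.5, D = 9: the true difference is −0.10 × 9 × 0.5 = −0.45, against HLSJ. LOCF gives 0.10 × 9 × 0.25 = +0.225 (simulated +0.23). The sign reverses.
- k = 2, D = 6 to 10: the true deficit is 0.6 to 1.0 points. LOCF gives 0.

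**The case against.** The best counter-argument is that the harm is conditional. With equal and similar dropout the null rejection rate stays at 2.5% to 2.8%, and nothing in the article predicts that the arms will differ. A modest split within the planned average, 12% on HLSJ against 8%, gives only +0.11 to +0.21 points and 3.4% to 4.7% false superiority for declines of 6 to 10 points. That stands, and it is why the sizes above are scenarios and not forecasts. But 15% vs 5% also averages 10%, and balance cannot be guaranteed when the rule is written.

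A second point is that if withdrawal follows deterioration closely, the false-superiority rate need not rise: at k = 2 the LOCF estimate is about zero. This is correct, so the 6.6% to 12.7% figures belong to the equal-progression case only. The error itself, Δ × D × k/2, grows with k. LOCF then conceals a deficit instead of creating a benefit.

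Other limits also stand.

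- Applying LOCF to deaths is a reading of the text, which names no separate rule.
- Entry criteria select milder patients, and withdrawal for deterioration is at the investigator's discretion.
- Patients with no post-baseline evaluation leave the analysis set and are not carried forward.
- The Discussion cites 25% of trial participants without decline over 6 months, so the bias holds on average and not for each patient.
- The standard-error point is minor here: with equal dropout the simulated rejection rate stays close to nominal.

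The unseen analysis plan may contain sensitivity analyses. It would not alter the fact that the article fixes LOCF for the primary outcome.

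**Conclusion.** The concern holds and should be corrected before the analysis. The plan states a rule for its confirmatory test that can create, hide or reverse a treatment difference when dropout differs between arms in amount, timing or rate of progression.

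At the planned 10% average dropout, split 15% to 5%, the bias is 15% to 30% of the 2.0-point design effect (0.30/2.0 to 0.60/2.0). At 30% vs 10% it reaches 0.6 to 1.2 points, or 30% to 60%, against a critical difference of 1.32. The amounts depend on the assumed decline and dropout split. The direction does not, provided the mean decline is positive and dropout timing is similar in the two arms.

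**What to change.** Replace LOCF in the primary analysis with a mixed model for repeated measures, or a constrained longitudinal model, on the observed ALSFRS-R at Weeks 12, 24, 36 and 48. Include treatment, visit, treatment-by-visit, baseline and baseline-by-visit, with an unstructured covariance. Keep the superiority rule and apply it to the Week 48 contrast.

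This model assumes data missing at random and does not define an outcome after death. Two analyses should therefore be pre-specified beside it:

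- a joint-rank analysis that places death or permanent ventilation below all survivors;
- a reference-based or delta tipping-point analysis for the other missing scores.

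LOCF can remain as a labelled historical sensitivity analysis, or be dropped.

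No new assessments are needed, since Table 2 already schedules every score. The cost is protocol and analysis-plan wording, ethics approval of the protocol update (section 4) and some programming. The change must be made before database lock, after which section 2.10.3 bars revision of the analysis plan, and by people who have not seen unblinded data, including any from the interim analysis in section 2.12.

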**Discussion:**

Here, we endeavored to evaluate TCM for ALS using a standard evidence-based approach for the first time. In addition, the ROADS, a self-report linear-weighted questionnaire, was selected as a secondary outcome measure. We expect to offer a new reference for the outcome evaluation of ALS trials.

**Clinical trial registration:**http://www.Chictr.org.cn, identifier ChiCTR2100044085.

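### Week 48 ALSFRS-R is imputed by LOCF while the secondary scales, including ALSFRS-R at Weeks 12 to 36, are not, so the results are not comparable like for like

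*Protocol article*

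**What the plan says.** The primary outcome in Section 2.9.1 is a single time point: "The primary outcome was the change in ALSFRS-R scores from baseline to Week 48". Section 2.9.2 makes the earlier visits of the same scale secondary ("Changes in ALSFRS-R from baseline to Week 12, 24, and 36") and lists ROADS at all four visits ("Changes in Rasch-Built Overall Amyotrophic Lateral Sclerosis Disability Scale (ROADS) scores from baseline to Week 12, 24, 36, and 48"). FVC %, ALSAQ-40 and SSCMS are listed at the same four visits.

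Section 2.10.3 gives two consecutive rules for missing data. For the primary: "The last observation carried forward (LOCF) method will be performed to impute missing values of the primary outcome measure". For everything else: "Missing values for secondary outcomes and safety will not be processed with a similar approach". No other method is named for the secondary outcomes. For the model itself, the primary uses ANCOVA on baseline ALSFRS-R plus Wilcoxon tests, and "A similar approach will be used to analyze the secondary outcomes".

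Section 2.10.2 assigns all efficacy evaluation to the full analysis set, and Section 2.10.3 invokes intention-to-treat. Section 2.11 lets the investigator withdraw a patient whose health deteriorates. Death, tracheostomy and permanent ventilation enter only as a separate endpoint (Section 2.9.2). The abstract says of the choice of ROADS as a secondary measure: "We expect to offer a new reference for the outcome evaluation of ALS trials".

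**The concern.** In a progressive disease the missing-data rule is part of what a result means. LOCF freezes a departed patient at an earlier, better score. An un-imputed analysis leaves that patient out. Using one rule for ALSFRS-R at Week 48 and the other for everything else has three consequences:

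- The ALSFRS-R series breaks. Weeks 12, 24 and 36 use patients assessed at that visit; Week 48 adds carried-forward values for those who left.
- Week 48 ROADS and ALSFRS-R differ in patients and in assumptions as well as in scale. If they disagree, the scale and the missing-data rule cannot be told apart.
- The un-imputed Week 48 comparison makes no use of what departed patients showed at Weeks 12 to 36, although those visits carry information on how fast they were declining. If faster decliners leave, and leave unequally by arm, the Week 48 contrast is biased.

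**Working it through.** **1. The plan's own figure.** Inputs from Section 2.10.1: difference 2.0, SD 4.0, two-sided alpha 0.05, power 80%, dropout 10%. The normal approximation, n = 2(z₀.₉₇₅ + z₀.₈₀)² × 4.0² / 2.0², gives 63 per arm. The t-test gives 63.77, so 64 per arm, with power 80.1%. 64 / 0.9 = 71.1, so 72 per arm and 144 in total. The stated sample size reproduces and is not at issue.

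**2. Which rule applies where.**

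| Outcome | Weeks 12, 24, 36 | Week 48 |
|---|---|---|
| ALSFRS-R | secondary, no LOCF | primary, LOCF |
| ROADS, FVC %, ALSAQ-40, SSCMS | secondary, no LOCF | secondary, no LOCF |

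**3. Patients contributing at Week 48, from 72 per arm.** LOCF uses up to 72, less anyone with no post-baseline evaluation. Un-imputed:
- 10% dropout (planned): 72 × 0.9 = 64.8
- 20% (assumed): 72 × 0.8 = 57.6
- 30% (assumed): 72 × 0.7 = 50.4

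At 20% loss the confidence interval is √(72/57.6) = 1.12 times as wide as with no loss, but only √(64.8/57.6) = 1.06 times as wide as at the loss already planned for.

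**4. Simulation with no true effect.** From the article: 72 per arm and SD 4.0. Assumed, not in the article: mean decline 8 points by Week 48, linear; dropout odds multiplied by e per SD of faster decline; last value at Week 12, 24 or 36; unequal dropout. The scale is ALSFRS-R points. Ranges cover repeat runs with small differences in set-up.

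| Dropout, HLSJ v riluzole | Un-imputed Week 48: bias | Un-imputed Week 48: type I error | LOCF Week 48: bias | LOCF Week 48: type I error | Repeated-measures likelihood: bias |
|---|---|---|---|---|---|
| 10% v 10% | 0.00 | 4.7–4.8% | – | – | – |
| 20% v 10% | 0.29–0.31 | 7.3–7.6% | 0.50–0.51 | about 13% | 0.12 |
| 25% v 10% | 0.45–0.48 | 9.1–10.3% | 0.75–0.76 | about 22% | 0.18 |

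On identical data the two rules in the plan differ by about 0.2 to 0.3 points (0.50 − 0.31 = 0.19; 0.75 − 0.46 = 0.29). At Week 24, in the two unequal scenarios, the un-imputed bias is only 0.03 to 0.06 with 5.2 to 5.4% rejection. The repeated-measures estimate keeps some bias because dropout here depends on the underlying slope, not only on observed scores.

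**5. Simulation with the planned true difference of 2.0.** Assumed: control decline 8 or 12 points and faster decliners leaving more often, so that the HLSJ arm loses fewer patients (4% when control loses 10%; 17% when control loses 30%).

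| Control dropout | Decline | LOCF estimate | Un-imputed estimate | Gap |
|---|---|---|---|---|
| 10% | 8 | 1.58 | 1.64 | 0.06 |
| 10% | 12 | 1.44 | 1.62 | 0.18 |
| 30% | 8 | 1.12 | 1.29 | 0.17 |
| 30% | 12 | 0.85 | 1.29 | 0.44 |

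Both rules understate the effect, and LOCF does so more.

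**The case against.** The article never says that secondary scales are analysed on observed cases. It excludes only a LOCF-like approach, and an unseen statistical analysis plan may name another method. That stands, and the by-visit un-imputed analysis is therefore called the plain reading and not a quoted rule. It does not remove the point: the text itself fixes different treatment for the primary and the secondary outcomes.

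A reader might go further and infer that the secondary results describe only survivors and completers and cannot be compared with the primary at all. The article does not support that. Someone who leaves after Week 24 still counts at Weeks 12 and 24, so the completer description fits Week 48 alone. At the planned 10% dropout the two rules differ by only about 0.1 to 0.2 point, and with equal dropout there is no false benefit. The article also plans no formal contest between ROADS and ALSFRS-R: Section 3 leaves further verification of ROADS to future trials, and the abstract expresses a general expectation.

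It is also fair that declining to use LOCF for the secondary scales is the better of the two choices, since LOCF is the more biased rule in every set-up with progression-related dropout above. Finally, a mixed model applied to the secondary scales alone would not restore comparability, and it does not define a score after death. Both objections are accepted and shape the fix.

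**Conclusion.** The concern holds in a limited form. As written, Section 2.10.3 gives ALSFRS-R one missing-data rule up to Week 36 and another at Week 48, and gives Week 48 ROADS a different rule from Week 48 ALSFRS-R. These results are not comparable like for like.

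The un-imputed Week 48 analyses can show a false difference of about 0.3 to 0.5 points with 7 to 10% type I error. That size depends on assumptions outside the article: unequal dropout of 20% v 10% or 25% v 10%, concentrated in faster decliners, with an 8-point decline. Section 2.11 makes progression-related withdrawal plausible, but nothing in the article predicts an imbalance between arms. Under equal 10% dropout there is no false difference, and at earlier visits the distortion is small. The point affects the reading of secondary results and of the ALSFRS-R trajectory. It is no reason to extend LOCF.

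**What to change.** Analyse each repeated scale (ALSFRS-R, ROADS, FVC %, ALSAQ-40, SSCMS) with one mixed model for repeated measures over Weeks 12 to 48 in the full analysis set. Include baseline value, treatment, visit and treatment-by-visit, use all observed visits, and report each visit's contrast from that model.

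Take Week 48 ALSFRS-R from the same model, either as the primary analysis or at least as a prespecified companion to the LOCF ANCOVA. It then continues the Week 12 to 36 series and can be set beside ROADS.

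State how deaths are handled in a sensitivity analysis, because the mixed model does not settle this by itself.

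The cost is wording and some added, largely shared, program code; no extra data are needed. The model rests on a missing-at-random assumption and reduces the bias without removing it (0.12 and 0.18 points in the two unequal scenarios above). Section 2.10.3 rules out revising the analysis plan after database lock, so the change has to be made before then.

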### 2.11. Withdrawal criteria

Consent withdrawal or loss to follow-up means that the subjects withdrew from the trial.

For some reason, the subject is no longer suitable for the current trial. The investigators have the discretion to withdraw the subject from the trial if the following conditions occur:The health of the patient deteriorates or some serious complications occur.Abnormal liver function with one of the following conditions present: (1) ALT or AST >8 times the ULN; (2) ALT or AST >5 times the ULN for 2 weeks; (3) ALT or AST >3 times the ULN, with total bilirubin >2 times the ULN or INR >1.5; (4) ALT or AST >3 times the ULN, with the following conditions: fever, rash, nausea, vomiting, severe fatigue, right upper abdominal pain, and/or percentage of eosinophilic granulocyte increased (>5%).Neutrophile granulocyte in blood <2.0 × 10^9^/L.Some special physiological situation, such as a female who becomes pregnant.Allergy or serious adverse reaction.Subjects unblinded during the trial (except SUSAR).Other conditions, such as the subject refuses a necessary nasal feeding tube or gastrostomy.

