### 2.6. Blinding procedures

The current trial was designed as a double-blind (participant- and investigator-blind) treatment. The similarity of HLSJ and its placebo in terms of both granules and solution status was proven in a previous study (Wu et al., 2021). Riluzole and placebo were indistinguishable in appearance and packaging. IMP is provided by the sponsor and then packaged and labeled by authorized people not participating in the observation, monitoring, and statistical analysis.

The randomization lists and parameters for randomization, such as the random seed and block length, are sealed and kept safe by the principal investigator and sponsor. A code revealing the assignment for a specific subject cannot be opened during the study unless the subject’s therapy assignment is necessary for the choice of treatment. The patient will withdraw from further participation in the study if his code is broken. One exception is that in the event of suspected unexpected serious adverse reactions (SUSAR), the Pharmacovigilance Division may unilaterally unblind a single case according to the submission requirements of the administration, with all others remaining blind. The SUSAR subject will not be considered to have dropped out.

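### Withdrawal for deterioration, toxicity or a code break ends trial participation, and the article provides no efficacy follow-up afterwards, so missing outcomes can depend on prognosis and on arm

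*Protocol article*

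**What the plan says.** Section 2.11 of the protocol article sets the general rule: "The investigators have the discretion to withdraw the subject from the trial if the following conditions occur". The object is the trial, not the study medication, and the rule is permissive. The listed conditions begin with "The health of the patient deteriorates or some serious complications occur" and go on to liver and neutrophil values, pregnancy, allergy or serious adverse reaction, and unblinding other than for a SUSAR. They close with "Other conditions, such as the subject refuses a necessary nasal feeding tube or gastrostomy".

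Section 2.6 is stricter on unblinding: "The patient will withdraw from further participation in the study if his code is broken". It exempts one case: "The SUSAR subject will not be considered to have dropped out".

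On analysis, section 2.10.3 declares intention-to-treat, imputes missing primary outcome values by LOCF, and does not apply a similar approach to secondary outcomes. Section 2.10.2 limits the full analysis set to randomised patients with at least one dose and at least one post-baseline efficacy evaluation. By Table 2, the first such evaluation is scheduled at Week 12.

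The only continued follow-up described for a patient with a problem is in section 2.9.3: adverse events are followed until stable. That is safety follow-up.

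**The concern.** Deterioration is what the primary outcome (ALSFRS-R decline, section 2.9.1) and the endpoint events (death, tracheostomy, permanent assisted ventilation, section 2.9.2) measure. A rule that lets a patient leave the trial for deteriorating makes missingness depend on the outcome. It sets no threshold, so practice may vary across the 11 centres. It also sits uneasily with section 2.8, which recommends supportive care for patients whose condition worsens during the study and so expects them to remain.

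The laboratory and reaction conditions follow drug tolerability. The arms receive different active drugs, so equal withdrawal cannot be presumed.

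The stated analysis does not repair this. LOCF holds a declining patient at an earlier score. Patients withdrawn before any post-baseline evaluation are not analysed for efficacy. If event status is not sought after withdrawal, the log-rank comparison treats patients at high risk as if their censoring were uninformative.

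**Working it through.** **1. The plan's own figure.** Inputs from section 2.10.1: difference 2.0, SD 4.0, two-sided alpha 0.05, power 80%, dropout 10%.

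- Normal approximation: n = 2 × (1.960 + 0.842)² × 4² / 2² = 62.8, so 63 per group.
- Two-sample t-test: 63.8, so 64 per group, with power 0.801.
- Dropout: 64 / 0.90 = 71.1, so 72 per group and 144 in total.

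The stated 64 and 144 reproduce. Nothing below disputes them.

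**2. What happens to a withdrawn patient under the stated rules.**

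- Withdrawn before any post-baseline efficacy evaluation: outside the full analysis set.
- Withdrawn later: in the full analysis set, with the last ALSFRS-R (Week 12, 24 or 36) standing in for Week 48.
- Endpoint events after withdrawal: no provision for collecting them is described.

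**3. Illustrative bias from LOCF.** The following are assumptions, not figures from the document: no true effect, a linear decline of 10 points over 48 weeks in both arms, and withdrawal unrelated to the patient's own slope. The SD of 4 is the plan's, and all 72 per arm are analysed.

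- False benefit = (excess proportion withdrawn on HLSJ) × 10 × (1 − last week / 48).
- Standard error = 4 × √(2/72) = 0.667.
- Chance of falsely declaring superiority = 1 − Φ(1.96 − false benefit / 0.667), nominally 2.5%.

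Worked case: a 10-point excess with last value at Week 12 gives 0.10 × 10 × 0.75 = 0.75 points. Then 0.75 / 0.667 = 1.125, and 1 − Φ(0.835) = 20%.

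| Last value | 5 points' excess | 10 points' excess | 15 points' excess |
|---|---|---|---|
| Week 12 | 0.38 (8%) | 0.75 (20%) | 1.13 (39%) |
| Week 24 | 0.25 (6%) | 0.50 (11%) | 0.75 (20%) |
| Week 36 | 0.13 (4%) | 0.25 (6%) | 0.38 (8%) |

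Cells show false benefit in ALSFRS-R points and, in brackets, the chance of false superiority. An excess of 10 points is about 7 patients (0.10 × 72 = 7.2). An excess on riluzole reverses the sign.

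**4. Withdrawal of the fastest decliners.** This was simulated with the same assumed decline and SD. With 15% withdrawn on HLSJ and 5% on riluzole, the false benefit is about 1.1 points (45% false superiority) from Week 12 and about 0.7 points (31%) from Week 24. With 10% withdrawn in each arm at the same time, there is no false benefit, and a true 2.0 points shrinks to about 1.9.

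**The case against.** **Section 2.11 is discretionary.** A reader might infer that every patient who deteriorates or has an abnormal value is removed. The text does not support that; such patients may be withdrawn. Only the code break in section 2.6 is worded as an obligation, and even that differs from section 2.11, which lists unblinding among the discretionary conditions. The two sections should be reconciled.

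**The article is silent rather than prohibitive.** It condenses a fuller protocol, which may describe early-termination visits. It nowhere says that outcomes cease to be collected, and it gives no censoring rule. This stands as a limit on certainty. What the article does state, however, is withdrawal from the trial or study, and it counts only the SUSAR case as not having dropped out.

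**Intention-to-treat is not flatly contradicted.** A reader might infer that withdrawn patients vanish from the analysis. Those with a post-baseline evaluation stay in the full analysis set through LOCF. The weakness lies in outcomes not collected and in patients lost before any evaluation.

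**A large loss of events cannot be claimed.** It is tempting to read the median survival of 2–4 years in section 1 as an exponential rate: 1 − 0.5^(0.92/4) = 14.7% to 1 − 0.5^(0.92/2) = 27.3% deaths in 48 weeks, or 21 to 39 of 144. One might then suppose that the 14 expected dropouts (0.10 × 144) take many of these events with them. Neither step holds. Section 2.3 selects milder patients (no ALSFRS-R item below 2, full respiratory items, FVC at least 70%). The 10% is an overall allowance, and section 2.11 also counts consent withdrawal and loss to follow-up as withdrawal.

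**The SUSAR exemption may have a reason.** Section 2.6 has the pharmacovigilance unit open a single code for regulatory submission while the rest remain blind. If that means other people, the site rater stays blind, whereas a code opened to choose treatment reveals allocation at the site. The phrase is ambiguous, so the exemption cannot be called arbitrary. A rater's knowledge is a reason to flag later assessments, not to stop collecting them.

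**Conclusion.** The point holds in a limited form. The article permits withdrawal from the trial for reasons tied to the outcome and to tolerability, requires it after a code break other than for a SUSAR, and provides no efficacy follow-up afterwards. LOCF then fills the gap with an earlier, usually better, score. This weakens the declared intention-to-treat principle and leaves the primary comparison open to bias if withdrawal differs between arms.

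Neither direction nor size can be fixed from the document. Under the assumptions in step 3 of the working, a 10-percentage-point excess on HLSJ gives a false benefit of 0.25 points (last value Week 36) to 0.75 points (last value Week 12), against a design effect of 2.0, and a false-superiority chance of about 6% to 20% against 2.5%. Withdrawal equal in proportion and timing gives no false benefit. The larger figures in step 4 need a strongly unequal and selective pattern that nothing in the document predicts.

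**What to change.** Leave the criteria for stopping study medication unchanged. Add that stopping medication or opening a code does not end follow-up unless the patient withdraws consent, and bring sections 2.6 and 2.11 into line on this. Then:

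- Keep collecting ALSFRS-R at Weeks 12, 24, 36 and 48 in these patients. Section 2.7 now accepts phone or video assessment only when COVID-19 travel restrictions prevent a site visit; extend that option to them.
- Ascertain death, tracheostomy and ventilation status at Week 48 for every randomised patient, retrospectively where consent allows for those already withdrawn.
- Include these data in the primary analysis, whatever the reason for unblinding.

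The cost is a short amendment and some extra remote assessments. They do not fit into the existing calls, which fall at Weeks 4, 8, 16, 20, 28, 32, 40 and 44. The sample size stays at 144. There is one limit: section 5 puts the end of enrolment in May 2022 and the last visits in May 2023, so ALSFRS-R assessments already missed cannot be recovered. Event status still can be sought.
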